# Effectiveness of exercise rehabilitation on aplastic anemia patients receiving hematopoietic stem cell transplantation: study protocol for a randomized controlled trial

**DOI:** 10.1186/s13063-024-08197-4

**Published:** 2024-06-05

**Keywords:** Aplastic anemia, Effectiveness, Exercise rehabilitation, Hematopoietic stem cell transplantation, Quality of life, Randomized controlled trial

## Abstract

**Background:**

Although hematopoietic stem cell transplantation provides the chances of survival for aplastic anemia patients, it is also related to many treatment-related physical and psychological side effects that severely influence the quality of life. Exercise interventions have shown positive results in mixed hematology populations. The study aims to determine the effectiveness of exercise rehabilitation in improving the quality of life, fatigue, and physical function in these patients.

**Methods:**

The study will enroll a total of 82 aplastic anemia patients receiving hematopoietic stem cell transplantation. They will be randomly divided into two groups in a 1:1 ratio. The intervention group will participate in structured exercise rehabilitation (plus usual care), while control group participants will receive usual care. The exercise rehabilitation program will be performed from neutrophil and platelet engraftment until 100 days after transplantation. All outcomes will be measured at the following time points: the neutrophil and platelet engraftment (± 1day, T0), discharge from the transplantation module (± 1 day, T1), hospital discharge (± 1 day, T2), and 100 days post-transplantation (± 5 days, T3).

**Discussion:**

This study aims to assess the effectiveness of exercise rehabilitation for aplastic anemia patients receiving hematopoietic stem cell transplantation in a Chinese single center. It is particularly vital to conduct the studies in this population. Moreover, the evidence obtained from the study will provide evidence for future research and clinical practice to exercise in aplastic anemia patients.

**Trial registration:**

ChiCTR2200060762. Registered on May 2022, www.trialregister.nl/trial/7702.

**Supplementary Information:**

The online version contains supplementary material available at 10.1186/s13063-024-08197-4.

## Background

Aplastic anemia (AA) is a bone marrow failure syndrome featured by pancytopenia associated with an empty or fatty bone marrow [1]. In addition, it is a non-malignant hematologic disorder that can mostly result in anemia, bleeding, and infection [2]. The incidence of AA in Asia, especially in East Asia, is around 2-3 times higher than that in Western countries. As a large population country, the annual incidence of AA in China is approximately 7.4 per million, which should not be underestimated [3]. Currently, hematopoietic stem cell transplantation (HSCT) is an effective method to achieve a radical cure for this disease. With the maturation of transplantation techniques, expanded indications for transplantation, and improved pretreatment protocols, the number of HSCT has been on a continuous increase globally for decades [4]. As shown in the Asia Pacific Blood and Marrow Transplantation (APBMT) report, China has the second largest number of hematopoietic stem cell transplants in the Asia-Pacific region with the fastest-growing number of transplants in the region [5]. Data from the Chinese Blood and Marrow Transplantation Registry (CBMTR) demonstrated that the number of HSCT for AA (HSCT-AA) patients continues to increase. Since 2012, it has surpassed myelodysplastic syndrome (MDS) to rank third in terms of number, after acute myeloid leukemia (AML) and acute lymphoblastic leukemia (ALL) [6]. In other words, AA has become the third most common indication for HSCT. Therefore, the population of these patients deserves more clinical and research attention.

According to studies, HSCT-AA patients had a survival rate of over 85% at 10 years [7, 8], and 96% of those who survived at 25 years were in complete remission at the last follow-up visit [9]. However, it should not be overlooked that HSCT is an aggressive and demanding medical therapy. In addition, it requires conditioning regimens of high-dose chemotherapy combined with total body irradiation, followed by transfusion of donor-harvested bone marrow or peripheral blood stem cells, which can make a serious impact on the quality of life of AA patients [10]. This warns that it appears undesirable for researchers to concentrate only on the survival rate and complications of HSCT-AA patients. It is correlated with many treatment-related physical, psychological, and psychosocial side effects. This process may lead to high levels of fatigue, decreased balance, skeletal muscle strength, athletic ability, and physical functions [11]. High doses of radiotherapy cause a variety of problems for patients, including mouth ulcers, nausea and vomiting, diarrhea, dry mouth, and hair loss [12]. The closed treatment environment of the transplantation module isolates patients from the outside and creates negative emotions including helplessness, depression, loneliness, and even anxiety and depression [13]. After transplantation, patients recover from the disease, but are full of uncertainty about work, fertility, and the future, with reduced social interaction and difficulties in social return [14]. Therefore, it is of necessity to provide supportive care for HSCT-AA patients to alleviate the various problems associated with HSCT.

Currently, meta-analyses have confirmed the positive impact of exercise interventions on the physical and psychosocial functioning and quality of life of transplant patients [15, 16]. However, as evidenced by the diversity of interventions and mixed hematologic and cancer populations, most of the existing studies have methodological limitations [17]. A mixed sample including both malignant and non-malignant hematology disorders that received HSCT was selected for most studies. No subgroup analysis was performed to determine whether it was the same hematologic disease. The symptoms and treatment modalities of patients with different hematologic diseases show significant differences. For example, malignant hematologic diseases (like leukemia) have a high risk of recurrence after transplantation, and disease recurrence is the leading cause of death after transplantation [18, 19]. By contrast, benign hematologic diseases such as AA have a lower risk of recurrence after transplantation, and the leading cause of death after transplantation refers to complications including graft-versus-host disease (GVHD) [20]. These differences in clinical characteristics support the need for exercise rehabilitation intervention studies in the HSCT-AA population. Meanwhile, we believe that studies on exercise interventions for malignant hematological diseases [21], lymphoma [22], and MDS [23] are also underway. To our knowledge, there is limited published literature on exercise rehabilitation in HSCT-AA patients. It provides an opportunity to examine the effectiveness of exercise interventions in benign but severe hematologic diseases such as HSCT-AA. The study hypotheses are as follows: (1) compared to the control group, exercise rehabilitation will result in a greater improvement on QoL (primary hypothesis); (2) compared to the control group, exercise rehabilitation will result in a greater improvement in muscle strength; (3) compared to the control group, exercise rehabilitation will result in greater improvement on fatigue and hematological indicators.

## Trials design

We will perform a randomized, controlled, assessor-blinded trial. In this trial, we will assess the effectiveness of exercise rehabilitation on HSCT-AA. The trial is registered in the Chinese Clinical Trial Registry (ChiCTR2200060762). The complete form can be accessed online at https://www.trialregister.nl/trial/7702. Patients with HSCT-AA were randomly divided into two groups: an intervention group (structured exercise rehabilitation program as the main intervention) and a control group (usual care as the main intervention). All patients in this study will start the intervention at the time of neutrophil and platelet implantation (± 1 day, T0), which lasted until 100 days post-transplantation. All outcomes were measured at the time of neutrophil and platelet engraftment (± 1 day, T0), discharge from the transplantation module (± 1 day, T1), discharge from the hospital (± 1 day, T2), and 100 days post-transplantation (± 5 days, T3). The study flow chart is displayed in Fig. 1.

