### Intervention

The intervention group received a structured exercise rehabilitation program, which was mainly developed by our team through preliminary literature research and by inviting experts in the relevant fields (including hematologists, nurses, and rehabilitation therapists) [24]. The exercise rehabilitation was divided into 3 phases according to the different periods of the patient’s transplantation; each phase involved warm-up, formal, and finishing exercises, and was tailored according to the strength of each participant.Phase 1: Exercise rehabilitation in the transplantation module (neutrophil and platelet engraftment to out of the transplantation module). Considering that the patient was weak in the early post-transplantation period, exercises in this phase were mainly bed and bedside activities. The warm-up exercises were mainly lip reduction-abdominal breathing with progressive relaxation exercises (involving hand muscles, arm muscles, hip muscles, thigh muscles, calf muscles, and toe muscles), for exercising the muscles of the whole body; the aerobic exercises in formal exercises were mostly performed with bed-side bicycles; the resistance exercises were mainly bed or bedside elastic band exercises performed by the patient (involving biceps, triceps, psoas major, abdominal, gluteal and foot muscles); and the finishing exercises wrapped up with progressive relaxation exercises.Phase 2: Exercise rehabilitation in the hematology ward (during admission to the general ward).

Patients who were transferred from the transplant module were in better condition than before, so it was appropriate to increase the intensity of exercises and move from bed to floor. The warm-up exercise included 6 movements (including head exercise, shoulder circuit, chest expansion, waist circuit, knee circuit, and wrist and ankle exercises) to avoid injury during exercise; the aerobic exercise options for formal exercises included Baduan Jin and Tai Chi; the resistance exercise was a stretch band exercise consisting of 8 movements (more difficult than before); and the finishing exercise was a relaxing stretch of the whole body in 8 movements from head to toe.Phase 3: Out-of-hospital exercise rehabilitation (post-discharge to 100 days post-transplantation).

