#### Adherence

In addition, an exercise rehabilitation log was issued to the participants during the exercise period. The exercise log, which was required to be recorded faithfully each day, covered several aspects including type and duration of exercises, subjective exercise responses (like the assessment of pain, fatigue, emotional state, and distress), and adverse events. When no exercise was performed, the reason should be provided. The first two phases of exercise rehabilitation were supervised by the interventionists, while the third phase of out-of-hospital exercise rehabilitation was supervised by daily WeChat exercise punch cards and weekly telephone contact. The exercise rehabilitation program was from the participant’s neutrophil and platelet engraftment after transplantation (approximately 14 days post-transplantation) to 100 days post-transplantation.

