### Primary and secondary outcomes

In this study, participants’ QoL was the primary outcomes, whereas participants’ muscle strength, fatigue, hematological indicators, exercise adherence, and adverse events were the secondary outcomes. All outcomes were measured at the time of neutrophil and platelet engraftment (± 1 day, T0), discharge from the transplantation module (± 1 day, T1), discharge from the hospital (± 1 day, T2), and 100 days post-transplantation (± 5 days, T3). Evaluations of T0 will be administered by the [name] enrolling the patient as part of the baseline assessment. Follow-up evaluations will be administered by [name], who are blinded to the patient’s group allocation. All assessors will be trained by the rehabilitation therapist on the steering committee before the start of the trial, and periodic meetings between the evaluators will be established fortnightly to promote internal transparency and consolidate data collection procedures. T0, T1, and T2 measurements will be performed in the inpatient of hematology, and T3 measurements will be performed in the inpatient or outpatient clinic of hematology, depending on the patient’s follow-up results.

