## Statistical analysis

SPSS26.0 was adopted for statistical analysis of data. Missing data were filled in using the Last observation carried forward (LOCF) and statistical analysis was conducted following the intention-to-treat (ITT) principle. Statistical tests were carried out with two-sided tests and *P* 0.05 was considered a statistically significant difference. Gender, education level, marital status, exercise adherence, and incidence of adverse events were described as frequencies and percentages. In the meantime, age, duration of AA, time to HSCT and QoL, muscle strength, fatigue, PLT, Neu, HB, and Ret counts were described as means and standard deviations if they conformed to normal distribution, or median if they conformed to non-normal distribution. The chi-square test or *t-*test was employed to compare differences between the intervention and control groups. Taking into account the potential variations in age, gender, and education level, analysis of variance (ANOVA) was conducted to assess the development of outcomes over time. Additionally, repeated measures analysis was used to analyze scores at baseline and follow-up scores of all measures.

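### T1 and T2 fall at discharge, which the intervention could move; between-arm conclusions should rest on the fixed day-100 visit, not on a test pooled over visits

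*Protocol article*

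**What the plan says.** **Visit definitions.** Trials design sets T1 at "discharge from the transplantation module (± 1 day, T1", T2 at "discharge from the hospital (± 1 day, T2" and T3 at "100 days post-transplantation (± 5 days, T3". The window of one day at T1 and T2 lies around an event; it does not fix a time since transplant. T0 is also an event, engraftment, which the Adherence section puts at "approximately 14 days post-transplantation". But T0 is the baseline, before exercise begins.

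**Order of events.** The Intervention section runs phase 1 from "neutrophil and platelet engraftment to out of the transplantation module", phase 2 through the general ward stay, and phase 3 from discharge to day 100. T1 and T2 are thus the ends of the first two exercise phases. The same section describes patients who have left the module as fitter than they were inside it.

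**Outcomes.** Primary and secondary outcomes applies the visit schedule to everything: "All outcomes were measured at the time of neutrophil and platelet engraftment (± 1 day, T0", and then at T1, T2 and T3.

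**Analysis.** Statistical analysis plans ANOVA for the course of outcomes over time, taking age, gender and education into account, and adds that "repeated measures analysis was used to analyze scores at baseline and follow-up scores of all measures". Missing values are filled by LOCF. Neither days since transplant nor length of stay is mentioned, and the article names no primary time point.

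**The concern.** Randomisation makes the arms comparable at a given time since transplant. It does not make them comparable at a milestone that each patient reaches after allocation, if treatment can change when the milestone is reached.

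The study hypotheses say that exercise improves strength, fatigue and blood counts as well as QoL. If that recovery also brings discharge forward, exercisers are assessed earlier, with fewer days of natural recovery behind them, and part of the benefit at T1 and T2 is hidden. If exercise delays discharge, the benefit is inflated. In both cases a T1 or T2 difference combines an effect on the outcome with an effect on timing.

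This would matter little if the conclusion rested on day 100. The planned analysis instead covers all visits for all measures, and nothing in the article singles out T3. An overall group test averages the discharge-timed visits with T3. A group-by-time test could be significant merely because the arms were measured on different days.

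**Working it through.** **1. The plan's own figure.** Inputs from the Sample size section: difference 12.3, SD 17.6, two-sided alpha 0.05, power 0.80.

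n per group = 2 × [(1.960 + 0.842) × 17.6 / 12.3]² = 32.1, rounded up to 33. This matches the stated 33. With the planned 41 per group, power for 12.3 points is 0.878 (two-sample t-test). The sample size is not in question here; 12.3, 17.6 and 41 serve only as yardsticks.

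**2. Shift at a discharge-timed visit.** The article gives neither the rate of QoL recovery nor the length of stay, so both are assumed: recovery of 1 to 3 points per week, and a between-arm difference of 3 to 10 days in reaching the visit. The formula treats the score as rising steadily with elapsed time.

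Shift = points per week × days / 7

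| Recovery (points/week) | Difference (days) | Shift (points) | Share of 12.3 |
|---|---|---|---|
| 1 | 3 | 1 × 3/7 = 0.43 | 3.5% |
| 2 | 7 | 2 × 7/7 = 2.00 | 16% |
| 3 | 10 | 3 × 10/7 = 4.29 | 35% |

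**3. Consequence for a T1 or T2 test.** With 41 per arm the standard error of a difference is 17.6 × √(2/41) = 3.89.

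- *Exercisers measured earlier.* A true 12.3 appears as 12.3 minus the shift, that is 11.87, 10.30 or 8.01 points. Power falls from 0.878 to 0.855, 0.745 or 0.531.
- *No true effect on the outcome.* The shift alone raises the two-sided rejection rate from 0.05 to 0.051, 0.080 or 0.193. A rejection in favour of exercise would come mainly from exercise delaying discharge.

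**4. Consequence for a pooled test.** If T1 and T2 shift equally and T3 does not, the mean over T1 to T3 shifts by (s + s + 0)/3 = 2s/3. For s = 0.43 to 4.29 this is 0.29 to 2.86 points, or 2.3% to 23% of 12.3. Pooling dilutes the problem but does not remove it.

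**5. Consequence for T3.** An observed T3 score is taken at day 100 ± 5 in both arms, so its shift is zero. LOCF changes this: a missing T3 would receive the T2 score, taken at a time that may differ by arm. If 20% of T3 values were filled in this way (the attrition allowance in the Sample size section), the T3 contrast would take on 0.20 × 0.43 = 0.09 to 0.20 × 4.29 = 0.86 points of the shift.

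**The case against.** **The visits fit the intervention.** T1, T2 and T3 close the three exercise phases, and outcome at the end of each care phase is a coherent randomised comparison. This stands, and is why T1 and T2 should be kept as supportive results. It does not justify pooling them with day 100 or reading them as effects at a common time.

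**The article does not say how time is coded.** It nowhere states that visits are treated as equal calendar times, and a separate analysis plan could use elapsed days or name T3. This stands as a limit. But the article does state the visit definitions, the methods, their application to all measures and the covariates, and on that text T1 and T2 are not set apart from T3.

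**Nothing shows that exercise moves discharge.** Correct. A reader might infer that the trial will be biased; the documents support only that it could be. The size in points is wholly assumed, and its low end, 0.43, is about 0.02 of the SD of 17.6.

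**T2 might fall after T3.** A reader might infer this from "T3 measurements will be performed in the inpatient or outpatient clinic of hematology". The sentence goes on to tie the setting to follow-up results, which fits readmission as well as a stay beyond day 100, and phase 3 presumes discharge before then. The text does not establish that the order reverses. Nor does it give a rule for a T2 that has not occurred by day 100.

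**Death in hospital.** A patient who dies before discharge has no T2 and usually no T3. That is a question of death and missing data, not of visit timing, and moving the inference to T3 does not settle it.

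**Conclusion.** The point holds in a limited form. T1 and T2 are post-allocation events whose timing the intervention could change, T3 is the only follow-up visit at a fixed time since transplant, and the stated analysis spans all of them without naming which one carries the conclusion. An overall group or group-by-time test would therefore mix the outcome effect with any timing effect.

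Under the assumed 1 to 3 points per week and 3 to 10 days, the shift at T1 or T2 is about 0.4 to 4.3 points, 3.5% to 35% of the planned 12.3. If the arms reach discharge at the same time, it is zero. If scores depend on fitness for discharge more than on elapsed days, the linear formula does not describe the bias and its size is unknown.

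Two stronger conclusions should not be drawn. T3 is not safe in every case: it is untouched when observed, but not when LOCF fills it from T2. Nor does putting actual days into a mixed model cure the problem by itself: if patients are assessed when judged well enough to leave, visit time carries information about the outcome.

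**What to change.** - **Main inference.** State that the confirmatory between-arm comparison for QoL, and the main comparison for each secondary outcome, is the model contrast at T3 (day 100) adjusted for the T0 value. Do not base the conclusion on a test pooled over visits.
- **T1 and T2.** Report them as supportive end-of-phase contrasts with confidence intervals, beside a table of days since transplant at each visit by arm. The reader can then see whether timing differed.
- **Missing visits.** Do not fill a T2 that did not occur, or a missing T3, by carrying an earlier discharge-timed score forward. Use a likelihood-based repeated measures model on the observed data. The handling of deaths needs its own statement.
- **Sensitivity.** A trajectory model in actual days since transplant may be added, with a note that visit timing may be informative.

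**Cost.** This changes analysis wording only; no visit, treatment or sample size changes. T1 and T2 lose confirmatory status, which gives up a formal test at the end of the two supervised phases. Visit dates must be recorded if they are not already; the article does not say that they are, although the visit windows presuppose them.

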**Fig. 1 Fig1:**
[figure not shown]
Flow chart of the study design

## Methods

### Study setting

This study will be conducted at a single site: The First Affiliated Hospital of Zhejiang Chinese Medical University (Zhejiang Provincial Hospital of Chinese Medicine). Recruitment and outcome evaluation of this study will be conducted in the outpatient clinic and ward of the Department of Hematology of the hospital. The exercise intervention implementation part consists of three parts: hospital transplantation module, hematology ward, and out-of-hospital home environment.

### Inclusion and exclusion criteria

The patient inclusion criteria were shown below: all patients with AA referred to the hospital for consideration of first HSCT, those aged 18 years or older, and those who were willing and able to offer written informed consent.

The exclusion criteria were as follows: those with communication problems, cognitive impairment, mental disorders, and inability to cooperate in completing credible investigations; those with severe heart, lung, liver, skeletal muscle, and kidney functional changes; those complicated by other serious diseases affecting exercise rehabilitation, such as DVT, pathological fracture, and spinal cord compression; those with vision problems that interfered with the smooth performance of exercises.

